#### Exclusion criteria

If a subject fulfills any of the following exclusion criteria, they may not be included:

Prior systemic treatment for mRCC.Major surgical procedure, open surgical biopsy, or significant traumatic injury within 28 days before enrollment.Other cancer within 5 years.Clinically significant (i.e., active) cardiovascular disease, for example, cerebrovascular accidents (< 6 months before inclusion), myocardial infarction (< 6 months before inclusion), unstable angina, and New York Heart Association (NYHA) grade II or greater congestive heart failure.No symptomatic brain metastasis requiring systemic corticosteroids (> 10 mg daily prednisone equivalent).Recent (within 30 days prior to inclusion) treatment with another investigational drug or participation in another investigational study.Any active or recent history of a known or suspected autoimmune disease or recent history of a condition requiring systemic corticosteroids (> 10 mg daily prednisone equivalent) or other immunosuppressive medications, excluding inhaled and topical steroids. Patients with vitiligo, type I diabetes mellitus, or residual hypothyroidism due to autoimmune thyroiditis requiring hormone replacement alone, and psoriasis not requiring systemic treatment are permitted to enroll.Oral or i.v. antibiotics administered 14 days prior to initiation of systemic therapy.Any positive test for hepatitis B- or C-virus indicating acute or chronic infection.Known hypersensitivity to monoclonal antibodies.Known history of testing positive for human immunodeficiency virus (HIV) or known acquired immunodeficiency syndrome (AIDS).Patients disagreeing to provide their human-derived materials.Vulnerable patients (such as children, prisoners, pregnant women, mentally disabled persons, or economically or educationally disadvantaged persons).Patients who cannot read and understand the consent form (such as individuals who are illiterate or foreigners).

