#### Group-specific criteria

Group A: Upfront CN: cytoreductive nephrectomy ± metastasectomy, followed by induction therapy with nivolumab plus ipilimumab, and maintenance therapy with nivolumab.

Group B: Deferred CN: cytoreductive nephrectomy ± metastasectomy after induction therapy with nivolumab plus ipilimumab, followed by maintenance therapy with nivolumab.

Group C: No surgery: induction therapy with nivolumab plus ipilimumab followed by maintenance therapy with nivolumab.

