### Study timeline

After completing the recruitment procedure, clinical and pathological data were collected (Table 1).

**Table 1 Tab1:** Clinical and pathological data

Clinical data				Pathological data
Baseline	Surgery-related	ICI therapy-related	Oncological outcome	
Age	OR note (including any intraoperative events)	Dosage	Overall survival	Pathological TNM staging
Sex	EBL	Cycle	Progression-free survival	Cell type
Height	Surgical morbidity (according to CDC)	Toxicities (graded by CTCAE v5.0)	Objective response rate (according to RECIST v1.1)	ISUP nuclear grade
Weight		Total administration periods		
BMI		Cause of discontinuation		
BSA				
KPS				
IMDC risk feature				
Clinical TNM staging				
Metastatic sites				

*BMI* body mass index, *BSA* body surface area, *CDC* Clavien–Dindo classification, *CTCAE* Common Terminology Criteria for Adverse Events, *EBL* estimated blood loss, *IMDC* International mRCC Database Consortium, *ISUP* International Society of Urologic Pathologists, *KPS* Karnofsky Performance Status, *OR* operating room, *RECIST* Response Evaluation Criteria for Solid Tumors

A flowchart of the study is shown in Fig. 1. Patients will be evaluated for eligibility for surgery. If they are not eligible for surgery, they will start ICI therapy (induction phase). Then, they will be assessed for whether they are eligible for surgery. If not, they will continue with ICI therapy (maintenance phase) (Group C). If they are eligible for surgery, they will be randomly allocated to the deferred CN group (Group B) or ICIs only. If they are eligible for surgery at the first visit, they will be randomly allocated to the upfront CN Group A (group A) or the deferred CN group (Group B). Patients will be randomly allocated in a 1:1 ratio using a computer-generated allocation sequence by a local project nurse. The randomization will be performed on an institutional basis to prevent bias.

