**Fig. 1 Fig1:**
[figure not shown]
Study flowchart. CN, cytoreductive nephrectomy; IMDC, International mRCC Database Consortium; Ipi, ipilimumab; mRCC, metastatic renal cell carcinoma; Nivo, nivolumab; KPS, Karnofsky performance status

Candidates for CN are patients with good performance status (Karnofsky performance status ≥ 80%) and less than three IMDC risk features and whose primary tumor could be surgically removed. Metastasectomy can be performed when the metastatic sites can be surgically removed. All patients eligible for ICI therapy will receive four cycles of intravenous nivolumab (3 mg/kg) plus ipilimumab (1 mg/kg) every 3 weeks as the induction phase, followed by a response evaluation. After the induction phase, intravenous nivolumab (3 mg/kg) will be administered 6 times every 2 weeks as the maintenance phase, followed by response evaluation. Nivolumab monotherapy will be maintained for a maximum of 2 years for those without adverse side effects. During ICI therapy, adverse events will be evaluated once per cycle. Patients will discontinue ICI therapy when they develop serious adverse events, including grade 3 or worse, according to the Common Terminology Criteria for Adverse Events version 5.0 (CTCAE v 5.0). In the upfront CN group, the induction phase will be within 6 weeks of surgery, whereas in the deferred CN group, surgery will be performed within 6 weeks of the induction phase. The study will be conducted over a period of 5 years.

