### Sample collection

Tumor tissue, blood, urine, and stool specimens for translational biomarker research will be sampled at the baseline visit, during surgery, 3 months after induction therapy, and 3 months after maintenance therapy. Embedded future studies will have their specific protocol and will obtain specific approval from the ethics committee separately. The tumor tissue from the participants will be obtained from a core needle biopsy sample (20 mg) or a surgically excised sample (1 g) of the viable tumor portion confirmed by the pathologist. Blood (10 mL for plasma) will be drawn when a medically required blood draw is present. Midstream urine (10 mL) and fecal (2–3 cc) samples will be collected from patients using the information leaflet provided. Samples will be collected 3–4 times, and an overview of the planned sample collection is shown in Tables 2, 3, and 4. All samples will be anonymously labeled with a pseudo-patient study identifier.

**Table 2 Tab2:** Study schedule of visits, and sampling of upfront cytoreductive nephrectomy group (Group A)

Time	0	*X*	*X* + 4 months	*X* + 7 months
Visit	Baseline visit	During surgery	After ICI induction phase (4 cycles)	After ICI maintenance phase (6 cycles)
Blood sample	O	O	O	O
Urine sample	O	O	O	O
Stool sample	O	O	O	O
Tumor tissue sample	O	O

**Table 3 Tab3:** Study schedule of visits, and sampling of deferred cytoreductive nephrectomy group (Group B)

Time	0	*X*	*X* + 3 months	*X* + 4 months	*X* + 7 months
Visit	Baseline visit	Before ICI therapy	After ICI induction phase (4 cycles)	During surgery	After ICI maintenance phase (6 cycles)
Blood sample	O		O	O	O
Urine sample	O		O	O	O
Stool sample	O		O	O	O
Tumor tissue sample	O			O

**Table 4 Tab4:** Study schedule of visits, and sampling of immune checkpoint inhibitor therapy group (Group C)

Time	0	*X*	*X* + 3 months	*X* + 6 months
Visit	Baseline visit	Before ICI therapy	After ICI induction phase (4 cycles)	After ICI maintenance phase (6 cycles)
Blood sample	O		O	O
Urine sample	O		O	O
Stool sample	O		O	O
Tumor tissue sample	O			

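### The antibiotic exclusion counts back from the start of systemic therapy, so at the first-visit randomisation it depends on the arm and, in Group A, generally cannot be settled before allocation

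*Protocol article*

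**What the plan says.** All references are to the protocol article.

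- **Exclusion criteria.** The list opens with "If a subject fulfills any of the following exclusion criteria, they may not be included", so each item is a condition of entry. The antibiotic item reads "Oral or i.v. antibiotics administered 14 days prior to initiation of systemic therapy". Other timed items use entry as the reference: "significant traumatic injury within 28 days before enrollment" and "Recent (within 30 days prior to inclusion) treatment with another investigational drug". The recent stroke and infarction items also count back from inclusion.
- **Study timeline.** "If they are eligible for surgery at the first visit, they will be randomly allocated to the upfront CN Group A" or to Group B. Patients unfit for surgery at that visit start immunotherapy without being randomised. Those who are fit after induction are then randomised between Group B and immunotherapy only.
- **Group-specific criteria.** "Group A: Upfront CN: cytoreductive nephrectomy ± metastasectomy, followed by induction therapy with nivolumab plus ipilimumab". Group B receives induction first and surgery afterwards.
- **Study timeline, text under Fig. 1.** "In the upfront CN group, the induction phase will be within 6 weeks of surgery".
- **Dropout criteria.** Patients who come to meet an exclusion criterion during the study are discontinued, and the need to start antibiotics is one of the examples given.
- **Statistical analysis** and **Adherence with study protocol.** Protocol violators are excluded from analysis, and non-adherent patients are dropped from the study.

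**The concern.** An entry criterion should be decidable before allocation and should mean the same thing in every arm. This one refers to a date that has not yet occurred at the first-visit randomisation and that the allocation itself shifts. Two patients with identical antibiotic histories can be classified differently only because of the arm they drew. An A patient can also become ineligible through something that happens after the operation.

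What is at stake is the A versus B comparison of overall survival. If patients are removed after randomisation because of antibiotic use following surgery, the removal is linked both to the arm and to the postoperative course. Randomisation does not protect against that kind of selection.

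**Working it through.** No figure stated in the protocol depends on this point, so the check sets the timing rules side by side.

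**1. When systemic therapy starts in each arm.** In B it is the first treatment, and the protocol sets no deadline for starting it. In A it follows surgery by at most 6 weeks, which is 42 days. The visit tables under Sample collection give a planned value:
- Table 2 (Group A) puts the post-induction visit at X + 4 months, where X is surgery.
- Tables 3 and 4 (Groups B and C) put it at X + 3 months, where X is the point before immunotherapy.
- Induction is four cycles at 3-week intervals, 4 × 3 = 12 weeks, or about 3 months, in every arm.
- The implied gap from surgery to systemic therapy in A is therefore 4 − 3 = about 1 month.

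**2. Where the 14-day window falls in A.** With a gap of about 30 days, the window covers roughly days 16 to 30 after surgery (30 − 14 = 16). At the 42-day limit it covers days 28 to 42 (42 − 14 = 28). Both lie wholly after randomisation and after surgery. The window reaches back to the day of surgery only if therapy starts within 14 days of it. The text permits that, but Table 2 does not plan it.

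**3. When the arms classify the same patient differently.** Let *a* be the days from the last antibiotic to randomisation, and let *g*_B and *g*_A be the days from randomisation to systemic therapy in each arm. Pre-randomisation antibiotics exclude the patient if *a* + *g* ≤ 14. The arms disagree when

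*a* + *g*_B ≤ 14 < *a* + *g*_A.

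The protocol gives none of these intervals, so the values below are assumptions that show the range.

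| *a* | *g*_B | *g*_A | B: *a* + *g*_B | A: *a* + *g*_A | Result |
|---|---|---|---|---|---|
| 10 | 0 to 3 | 14 to 42 | 10 to 13 | 24 to 52 | excluded in B, passes in A |
| 3 | 7 | 28 | 10 | 31 | excluded in B, passes in A |
| 10 | 7 | 14 to 42 | 17 | 24 to 52 | passes in both |
| 3 | 0 | 7 | 3 | 10 | excluded in both |

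With the gap of about one month from Table 2, *g*_A is at least about 30 days. No antibiotic given before randomisation can then count in A, whatever *a* is.

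**4. The reverse route.** An A patient with no antibiotics at baseline who receives them postoperatively, inside the window in step 2, meets an exclusion criterion after being randomised and operated on. A B patient has no operation before systemic therapy and so has no equivalent route at that stage.

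**5. The second randomisation.** For patients randomised after induction, systemic therapy began before allocation. The window is closed and known, so the arm dependence does not arise there.

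**6. How the other rules interact.** The Dropout criteria discontinue patients who need to start antibiotics during the study. That rule has no 14-day limit and applies in every arm. The Statistical analysis section then excludes violators. An A patient given postoperative antibiotics could therefore be lost under the dropout rule even if the entry criterion were re-anchored. The disagreement in step 3 has a different source: it concerns antibiotics taken before randomisation and stems from the entry criterion alone.

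**The case against.** The strongest reply is that most of the practical loss comes from the dropout rule rather than from the anchor date. This stands in part. Re-anchoring the exclusion without changing the Dropout criteria and the analysis rule would retain no A patient treated with postoperative antibiotics. It does not dispose of the point, because the entry rule would still be undecidable in A and would still treat pre-randomisation antibiotics differently in A and B.

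The pre-randomisation route is also narrow. It needs recent antibiotics and a prompt start in B, which the protocol does not require; Table 3 lists baseline and the visit before immunotherapy separately. If therapy in B is delayed, part of its window also falls after randomisation. In addition, the sample size rests on A and B combined against immunotherapy alone, so A versus B is not the contrast that was powered.

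A reader might infer three stronger things that the document does not support:
- **Nearly all A patients would be excluded because of antibiotics given at surgery.** This needs therapy within 14 days of surgery. Table 2 implies about one month, so antibiotics confined to the day of surgery would usually fall outside the window.
- **A specific loss, such as 1 to 4 patients in A against none in B.** That requires equal thirds (57/3 = 19) and an assumed antibiotic rate of 5 to 20% (0.95 to 3.8 patients). The two successive 1:1 allocations and the non-randomised entry to Group C do not fix A at one third, the protocol gives no rate, and B patients also have surgery later, when the dropout rule applies to them.
- **Baseline microbiome profiles are not comparable between A and B.** The baseline stool sample ("stool specimens for translational biomarker research will be sampled at the baseline visit, during surgery") is not covered by the window in A. Antibiotic use before randomisation is nevertheless balanced in expectation between the randomised arms. Imbalance would need selective later removal, whose extent is not shown.

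**Conclusion.** The point holds in a limited form. For patients randomised between A and B at the first visit, the antibiotic exclusion depends on the arm and in A generally cannot be assessed before allocation. Nothing elsewhere in the article re-anchors it. The conclusion about A rests on the protocol's own sequence of treatments and on the gap of about one month implied by Tables 2 to 4. The conclusion that pre-randomisation antibiotics can exclude a B patient but not an A patient also assumes a reasonably prompt start of therapy in B.

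The size of any bias cannot be given, because the document states neither antibiotic use nor the interval from randomisation to treatment. The dropout and analysis rules make the consequence worse, since a late-triggered exclusion can become a loss from the survival analysis. The point should be corrected. It is not evidence that the trial's main comparison is invalid.

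**What to change.** 1. Anchor the antibiotic exclusion to a date that is common to all arms and known before allocation. Enrolment or randomisation would match the other timed exclusions.
2. Reconcile the Exclusion criteria, Dropout criteria, Study timeline, Adherence and Statistical analysis sections, so that antibiotic exposure after allocation neither makes a patient retrospectively ineligible nor removes the patient from the overall survival analysis. Changing the exclusion alone is not enough.
3. Record antibiotic exposure with dates in all arms, for use in the microbiome analyses.

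The cost is a short amendment and a dated medication field. The small downside is that some exposure before immunotherapy will be recorded rather than excluded. Whether and how antibiotic use should affect treatment is a clinical matter for the investigators, and no rule on it is proposed here.

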#### Group-specific criteria

Group A: Upfront CN: cytoreductive nephrectomy ± metastasectomy, followed by induction therapy with nivolumab plus ipilimumab, and maintenance therapy with nivolumab.

Group B: Deferred CN: cytoreductive nephrectomy ± metastasectomy after induction therapy with nivolumab plus ipilimumab, followed by maintenance therapy with nivolumab.

Group C: No surgery: induction therapy with nivolumab plus ipilimumab followed by maintenance therapy with nivolumab.

### Study timeline

After completing the recruitment procedure, clinical and pathological data were collected (Table 1).

**Table 1 Tab1:** Clinical and pathological data

Clinical data				Pathological data
Baseline	Surgery-related	ICI therapy-related	Oncological outcome	
Age	OR note (including any intraoperative events)	Dosage	Overall survival	Pathological TNM staging
Sex	EBL	Cycle	Progression-free survival	Cell type
Height	Surgical morbidity (according to CDC)	Toxicities (graded by CTCAE v5.0)	Objective response rate (according to RECIST v1.1)	ISUP nuclear grade
Weight		Total administration periods		
BMI		Cause of discontinuation		
BSA				
KPS				
IMDC risk feature				
Clinical TNM staging				
Metastatic sites				

*BMI* body mass index, *BSA* body surface area, *CDC* Clavien–Dindo classification, *CTCAE* Common Terminology Criteria for Adverse Events, *EBL* estimated blood loss, *IMDC* International mRCC Database Consortium, *ISUP* International Society of Urologic Pathologists, *KPS* Karnofsky Performance Status, *OR* operating room, *RECIST* Response Evaluation Criteria for Solid Tumors

A flowchart of the study is shown in Fig. 1. Patients will be evaluated for eligibility for surgery. If they are not eligible for surgery, they will start ICI therapy (induction phase). Then, they will be assessed for whether they are eligible for surgery. If not, they will continue with ICI therapy (maintenance phase) (Group C). If they are eligible for surgery, they will be randomly allocated to the deferred CN group (Group B) or ICIs only. If they are eligible for surgery at the first visit, they will be randomly allocated to the upfront CN Group A (group A) or the deferred CN group (Group B). Patients will be randomly allocated in a 1:1 ratio using a computer-generated allocation sequence by a local project nurse. The randomization will be performed on an institutional basis to prevent bias.

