### Primary endpoint

The primary endpoint is OS (in months) compared between patients receiving upfront CN, deferred CN, and ICIs only.

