### Sample size justification

Two prospective RCTs, PROBE (NCT04510597) and NORDICSUN (NCT03977571), are currently ongoing, but do not include an upfront CN arm. We determined the sample size based on the most recent real-world data that analyzed the intermediate/high risk group of mRCC patients stratified into upfront CN, deferred CN, and systemic treatment group [17]. To determine the required sample size for the study, we utilized two calculators for two-group survival analysis [18]. For Calculator 1, with a two-tailed alpha level (*α*) set at 0.05 and a beta level (*β*) of 0.2, along with a proportion of subjects in Group 1 (upfront and deferred CN) of 0.66 and a proportion in Group 0 (ICIs only) of 0.34, the relative hazard was set at 0.37. The calculated number of events needed to achieve 80% power was 35. For Calculator 2, with the total number of events set at 35, and assuming a baseline event rate of 0.53 and a median survival time in Group 0 (ICIs only) of 1.3 years, along with a censoring rate of 0.1 and a planned average length of follow-up of 5 years, the sample sizes required for each group were determined. Therefore, a total of 57 subjects were needed for the study.

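### Patients ineligible for surgery at the first visit get a group only after ICI induction, so those who die or stop during induction have no stated group or OS start

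*Protocol article*

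**What the plan says.** All references are to the protocol article. Study timeline describes two entry routes.

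- **Eligible at the first visit:** randomised at once between A and B ("If they are eligible for surgery at the first visit, they will be randomly allocated to the upfront CN Group A (group A) or the"; the sentence closes by naming Group B). These patients have a group from the start.
- **Not eligible at the first visit:** "If they are not eligible for surgery, they will start ICI therapy (induction phase"). No group is named here. After induction they are reassessed. Those still ineligible: "If not, they will continue with ICI therapy (maintenance phase) (Group C"). Those now eligible: "If they are eligible for surgery, they will be randomly allocated to the deferred CN group (Group B) or ICIs only".

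Group-specific criteria defines the comparator in the same sequence: "Group C: No surgery: induction therapy with nivolumab plus ipilimumab followed by maintenance therapy with nivolumab". The text under Fig. 1 sets the length of induction: "four cycles of intravenous nivolumab (3 mg/kg) plus ipilimumab (1 mg/kg) every 3 weeks as the induction phase".

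Primary endpoint reads: "The primary endpoint is OS (in months) compared between patients receiving upfront CN, deferred CN, and ICIs only". No section says when the OS clock starts.

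Three further sections bear on patients who stop. Dropout criteria removes those whose side effects prevent treatment on schedule. Adherence with study protocol drops the non-adherent. Statistical analysis excludes subjects without endpoints or with protocol violations.

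**The concern.** Every described route into the ICI-only group passes through the post-induction assessment. A patient on the ICI-first route who dies before it is assigned nowhere in the text. One who stops before it is dropped from the study before receiving a label. Patients randomised at the first visit already belong to A or B when induction begins, so a death during induction falls after their allocation.

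This is the usual setting for survivor selection. If ICI-only consists of people who got through induction, and their survival is nevertheless counted from baseline, the group is credited with some three months in which its members could not die. Late-randomised Group B patients pass the same filter. At stake is which deaths enter the primary endpoint in a trial planned on 35 events. When and how a patient joins a comparison group is design, and this section fixes it, so an analysis plan could not repair it without changing the rule.

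**Working it through.** **Inputs (Sample size justification unless noted).** Two-sided α 0.05; power 80%; proportions 0.66 (upfront and deferred CN) and 0.34 (ICIs only); hazard ratio (HR) 0.37; 35 events; "a median survival time in Group 0 (ICIs only) of 1.3 years"; baseline rate 0.53 per year; censoring 0.1 per year; follow-up 5 years; 57 subjects. Induction is 4 cycles of 3 weeks: 9 weeks to the last dose, 12 weeks to the end of cycle 4 (about 3 months in Table 4).

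**Step 1: the plan's own figures.** Events by Schoenfeld: (1.96 + 0.84)² / (0.66 × 0.34 × (ln 0.37)²) = 35.4. With 35 events, power is 79.6%. The event probability is λ/(λ+c) × (1 − e^(−5(λ+c))). With c = 0.1 it is 0.805 for λ = 0.53 and 0.512 for λ = 0.37 × 0.53. Weighted: 0.34 × 0.805 + 0.66 × 0.512 = 0.611, and 35/0.611 = 57.2. The stated 35 and 57 reproduce and are not in dispute.

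**Step 2: deaths before assignment.** The hazard is ln 2/1.3 = 0.533 per year, agreeing with the stated 0.53.

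- 9 weeks: 8.8%
- 12 weeks: 1 − e^(−0.533 × 0.230) = 11.5%
- 3 months: 1 − e^(−0.533 × 0.25) = 12.5%
- 12 weeks, with an assumed median of 0.8 to 2.0 years: 18% to 8%

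The implied ICI-only group is 57 × 0.34 = 19.4. If 19.4 start, 19.4 × 0.115 = 2.2 die before assignment. If 19 are the survivors of 3 months, 19/0.875 = 21.7 started and about 3 died. Hence roughly 2 to 3.

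**Step 3: effect on the HR if these patients are omitted.** Exponential survival, 66:34 split, loss 0.1 per year, 5-year cut-off, ICI-only conditioned on surviving 12 weeks, all CN patients allocated at the first visit, large-sample Cox estimate:

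| True HR | OS from baseline | OS from allocation |
|---|---|---|
| 0.37 | 0.41 | 0.36 |
| 0.70 | 0.81 | 0.71 |
| 1.0 | 1.15 | 0.97 |

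With no omission the same simulation gives 0.37, 0.69 and 0.99, so the last column shows no bias beyond simulation error. Conditioning on 3 months instead of 12 weeks gives about 0.42 for a true 0.37.

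**Step 4: late allocation of CN patients.** Let half the CN patients pass the same 12-week filter. For a true HR of 1.0, compare events per person-year. A first-visit patient contributes 0.807 events over 1.513 years (rate 0.533). An induction survivor timed from baseline contributes 0.801 events over 0.230 + 1.502 = 1.732 years (rate 0.462). First-visit CN only: 0.533/0.462 = 1.15. Half late: (0.807 + 0.801)/(1.513 + 1.732) = 0.495, and 0.495/0.462 = 1.07. For a true 0.37, a Cox simulation with half allocated late gives about 0.39.

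**Step 5: unequal patients.** With assumed gamma frailty of variance 0.5 to 1.0 and OS from allocation, the estimate at a conditional HR of 0.37 moves from 0.45–0.49 with nobody omitted to 0.48–0.53. A smaller shift therefore survives even with the better time origin.

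**The case against.** The strongest reply is that the article never says these deaths are left out. The primary endpoint compares patients by what they received, and someone who dies during induction on this route received ICIs only. Table 4 starts the Group C schedule at the baseline visit, and the Discussion promises follow-up to death. This stands. A reader might infer that induction deaths are counted nowhere, but the documents support only that their group is unstated. Removal is written down only for those who stop, and those dropout and exclusion rules apply to every group.

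A reader might also infer that the comparator is made to look better overall. That does not follow. Patients who remain unsuitable for surgery enter Group C without randomisation; the article's candidacy criteria are performance status, number of risk features and a removable primary. This pulls against ICI-only. On the figures above, a hazard about 15% higher in such patients would roughly cancel the shift at a true HR of 1.0.

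Third, the largest shift needs OS from baseline and all CN patients allocated at the first visit. The randomised late comparison of B with ICIs only is not distorted, since both sides passed the same filter. The entry requirement of more than 4 months' life expectancy should also reduce early deaths below the exponential figure. All of this stands and limits the size.

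What the reply does not remove is the assignment rule itself. The sponsor must still say where these patients belong and when their survival time begins. Two opposing biases cannot be relied on to cancel.

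**Conclusion.** The point holds in a conditional form. Group membership on the ICI-first route is settled only after induction; deaths and stops before then have no stated group; the OS origin is unstated. If those patients are omitted and OS runs from baseline, this component alone favours ICI-only and late-randomised B over first-visit patients. The size is about 12% dying before assignment, with an HR of 0.37 appearing as up to about 0.42 and 1.0 as up to about 1.15. This rests on constant hazards, the protocol's 1.3-year median and all CN patients allocated at the first visit.

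A loss of power should not be claimed as a result. An apparent HR of 0.41 to 0.43 would cut power at 35 events from 79.6% to about 70–66%, but only in that worst case and with the opposing selection ignored. The net direction is open. The planned 35 events and 57 subjects are arithmetically unaffected.

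**What to change.** 1. Place every patient who is ineligible for surgery at the first visit in a named ICI-first cohort at enrolment, and keep all their deaths in it for OS, whether or not induction is completed.
2. Analyse the randomised comparisons separately, each with OS from its own randomisation and all randomised patients kept: A versus B from the first visit, and B versus ICIs only from the post-induction randomisation.
3. Label any comparison across the two entry routes as non-randomised, and time it from enrolment with induction deaths and stops included. The ICI-first cohort will contain some patients later randomised to B, so it is not itself the ICI-only arm.
4. Report induction deaths and stops in their own row, and state whether these patients count towards the enrolment target.
5. Restate the power claim for pooled CN versus ICIs only as not resting on a randomised comparison.

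Items 1 to 4 need protocol and analysis wording, with no new visits and no change to treatment. The cost is that the ICI-first cohort's survival will look less favourable, fewer patients will contribute to the randomised B versus ICIs-only comparison, and the headline power statement loses its present standing.
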